### Objectives

This paper presents the protocol for a pilot study designed to evaluate the feasibility, construct validity, and rating reliability of remotely administered physical function assessments in adults with ASD, with attention to racial and ethnic equity in participation and outcomes.

This study has three primary aims:

To evaluate the feasibility, construct validity, and rating reliability of remote physical function assessment in adults with ASD.
Construct validity will be examined primarily through hypothesis testing of the Patient-Reported Outcomes Measurement Information System–Physical Function (PROMIS-PF) measure against related indicators of health and functioning, including habitual PA, lower-extremity functional outcome surveys, fall risk screening surveys, and comorbidity burden. Remote performance-based measures will also be examined as exploratory complementary indicators of physical function. Interrater and intrarater reliability of remote performance scoring will be evaluated using video-recorded assessment sessions scored by multiple raters.To examine racial and ethnic disparities in physical function, PA, fall risk, and QoL among adults with ASD.
This objective is intended to generate preliminary evidence regarding differences in health and functioning across racial and ethnic groups within a telehealth-based study sample.To examine associations among physical function, PA, personal and environmental factors, and QoL, and to evaluate whether these relationships vary by race and ethnicity.
This objective will assess whether physical function and PA are associated with QoL and whether race/ethnicity moderates these relationships.

This protocol is intended to provide foundational evidence for more accessible, equitable, and scalable approaches to physical function assessment in adults with ASD. If the planned hypotheses are supported, the findings may inform future larger-scale studies and telehealth-based rehabilitation strategies aimed at improving physical function, PA, and QoL in this population.

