#### Aim 1: Construct Validity and Reliability of PROMIS-PF

Construct validity of the PROMIS-PF will be examined using a hypothesis-testing framework with related indicators of health and physical functioning consistent with COSMIN (Consensus-Based Standards for the Selection of Health Measurement Instrument) recommendations [59,60]. Predefined hypotheses were specified regarding both the expected direction and magnitude of associations. PROMIS-PF scores (higher scores indicate better perceived physical function) are expected to demonstrate:

Moderate-to-strong positive correlations with other self-reported measures of physical function (eg, LEFS and PROMIS Global Health; r≈0.50-0.70)Moderate positive correlations with habitual PA (steps/day; r≈0.30-0.50)Small-to-moderate negative correlations with comorbidity burden and fall risk indicators (r≈−0.20 to −0.50), where higher scores reflect poorer status.

Associations will be examined using Pearson correlation coefficients when parametric assumptions are met and Spearman rank correlations when assumptions are violated. Correlation coefficients will be reported with 95% CIs, and the interpretation will emphasize agreement with a priori hypotheses [60]. Correlations between PROMIS-PF and other self-report instruments (eg, LEFS and PROMIS Global Health) will be interpreted with caution, as these comparisons are subject to shared method variance, which may inflate associations due to common response tendencies rather than true construct overlap. Accordingly, these analyses will be considered supportive but weaker evidence of convergent validity.

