Greater emphasis will be placed on the associations between PROMIS-PF and objective remote performance-based measures, which provide stronger evidence of construct validity due to reduced susceptibility to shared measurement bias. However, these comparisons are limited to a subset of 25 participants and will be interpreted as exploratory. These remote performance-based measures include the 5xSTS, the 30sSTS, and the Standing SLS test under EO and EC conditions. PROMIS-PF scores are expected to correlate negatively with 5xSTS completion time (r ≈ −0.40 to −0.70) and positively with 30sSTS repetitions and SLS duration (r≈0.40-0.70), such that better self-reported function corresponds to better observed functional performance and balance [44,60]. Given the smaller subsample, these analyses will be considered exploratory and interpreted with appropriate caution due to wider CIs. Adjustment for multiple comparisons will be applied within related families of analyses as appropriate.

Reliability will be evaluated for rater-derived scores from recorded remote performance assessments (ie, reliability of scoring rather than repeat participant testing). All sessions will be video-recorded and independently scored by 6 raters to estimate interrater reliability. To estimate intrarater reliability, each rater will re-score the same recordings after a 2-5-day interval. Intraclass correlation coefficients (ICCs) with 95% CIs will be calculated using absolute-agreement models appropriate to the rating design. ICC values will be interpreted using standard thresholds: ≥0.90 (excellent), 0.75-<0.90 (good), 0.50-<0.75 (moderate), and <0.50 (poor) [61-64]. We hypothesize that repeated ratings of recorded remote performance assessments will demonstrate strong interrater and intrarater reliability (ICC ≥0.80).

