An a priori power analysis was conducted using G*Power (version 3.1.9.7; Heinrich Heine University Düsseldorf) [63]. Assuming a 2-tailed α=.05 and power=0.80, a total sample size of N=155 provides adequate power to detect small-to-moderate correlations (r ≥ 0.25-0.30), consistent with expected construct validity effect sizes. PROMIS-PF scores are expected to demonstrate moderate positive correlations with habitual PA and performance-based functional measures and moderate-to-strong positive correlations with other self-reported function scales. Negative correlations are anticipated with fall risk indicators and comorbidity burden. In addition to the power-based justification, precision was considered. At N=155, correlation estimates are expected to have reasonably narrow 95% CIs, supporting adequate precision in estimating associations [64].

The sample size for reliability analyses was informed by Borg et al [59]. Assuming 2 repeated measurements per rater, a subsample of n=25 is expected to provide sufficient precision to estimate ICC values ≥0.75, consistent with recommendations for reliability studies.

The full sample (N=155) will be used for primary construct validity analyses, while the nested subset (n=25) will support exploratory performance-based validity analyses and reliability estimation.

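### The Aim 1 power statement for N=155 is right for r of 0.25-0.30 but does not match two sets of the plan's own hypotheses, and it gives 5xSTS the opposite sign

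*Protocol article*

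**What the plan says.** All of this is in the Protocol article, mostly in the Aim 1 section of the Statistical Data Analysis Plan.

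- **Power.** "Assuming a 2-tailed α=.05 and power=0.80", the plan states that "a total sample size of N=155 provides adequate power to detect small-to-moderate correlations (r ≥ 0.25-0.30"), and describes this as in line with the effect sizes expected for construct validity. The next sentences list those effects, including: "PROMIS-PF scores are expected to demonstrate moderate positive correlations with habitual PA and performance-based functional measures". The paragraph ends by saying that confidence intervals at N=155 will be reasonably narrow.
- **Full-sample hypotheses.** One of the predefined sets is "Small-to-moderate negative correlations with comorbidity burden and fall risk indicators", with r of about -0.20 to -0.50.
- **Performance-test hypotheses.** "PROMIS-PF scores are expected to correlate negatively with 5xSTS completion time", with r of about -0.40 to -0.70. For 30sSTS repetitions and single-leg stance time the expected r is +0.40 to +0.70. These comparisons are limited to the nested 25.
- **Weight.** "Greater emphasis will be placed on the associations between PROMIS-PF and objective remote performance-based measures". The next sentence, and another further on in that paragraph, call these comparisons exploratory. The Objectives say: "Remote performance-based measures will also be examined as exploratory complementary indicators of physical function". The last paragraph of Aim 1 says: "The full sample (N=155) will be used for primary construct validity analyses", and leaves the exploratory performance-based validity analyses to the 25.

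**The concern.** Aim 1 judges validity by whether each correlation agrees with a direction and size fixed in advance. The power paragraph is where a reader learns how well the study can do that. It offers one figure, for N=155, and then names effects that this figure does not cover. One set is weaker than the stated floor of 0.25. The other is measured in 25 people, and no power or precision is given for correlations at that size; the n=25 rationale that follows concerns ICCs only. The paragraph also reverses the expected direction of one hypothesis. Under Aim 1 the 5xSTS correlation should be negative, because a shorter time is better (5xSTS section), yet the power paragraph expects performance measures as a group to correlate positively.

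Two things are at stake: the stated power for the plan's own hypotheses, and an unambiguous a priori sign for 5xSTS. The weight wording adds to this, because greater emphasis and exploratory status sit side by side with no statement of how they combine.

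**Working it through.** **Inputs (Aim 1).** Two-sided alpha 0.05, target power 0.80, N=155 for full-sample correlations, n=25 for performance tests. Hypothesised floors: |r|=0.20 (comorbidity, fall risk) and |r|=0.40 (performance tests).

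**Formulas (Fisher z).**
- Power = Φ(atanh(r)·√(N−3) − 1.960), plus a negligible opposite tail.
- N for 80% power = ((1.960 + 0.842)/atanh(r))² + 3, rounded up.
- Detectable r = tanh((1.960 + 0.842)/√(N−3)).
- 95% CI = tanh(atanh(r) ± 1.960/√(N−3)).

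**1. The plan's own figure.** √152 = 12.329.
- r=0.25: 0.2554 × 12.329 − 1.960 = 1.189, power 0.883. N for 80% power is 124.
- r=0.30: 0.3095 × 12.329 − 1.960 = 1.856, power 0.968. N for 80% power is 85.

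The stated figure is reproduced and is conservative. The detectable r at N=155 is tanh(2.802/12.329) = 0.223.

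**2. The weakest full-sample hypothesis, |r|=0.20.**
- 0.2027 × 12.329 − 1.960 = 0.539, power 0.705. The exact bivariate-normal model gives 0.708 and the point-biserial t model 0.714.
- N for 80% power = (2.802/0.2027)² + 3, which rounds up to 194 (193 by the exact model).

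**3. Performance tests at n=25.** √22 = 4.690.
- Detectable |r|: tanh(2.802/4.690) = 0.535; the exact model gives about 0.53.
- |r|=0.40: 0.4236 × 4.690 − 1.960 = 0.027.

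| True abs(r), n=25 | Fisher z | Exact | Point-biserial |
|---|---|---|---|
| 0.40 | 0.51 | 0.53 | 0.55 |
| 0.50 | 0.73 | 0.75 | 0.79 |
| 0.70 | 0.98 | 0.99 | 1.00 |

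For 80% power at |r|=0.40 about 47 people are needed (46 by the exact model).

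- 95% CI at r=0.40, n=25: tanh(0.4236 ± 0.4179) = 0.006 to 0.687.
- 95% CI at r=0.40, N=155: tanh(0.4236 ± 0.1590) = 0.259 to 0.525.

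The n=25 interval is 0.68 wide, against a hypothesised band of 0.30 (0.40 to 0.70).

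All these figures use unadjusted alpha. Aim 1 mentions multiplicity adjustment as appropriate. If that meant Bonferroni over four tests (my assumption; the number is not given), power at |r|=0.40 with n=25 would be about 0.31.

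**4. Sign.** The power paragraph says positive for performance measures as a group. The hypothesis earlier in Aim 1 says negative for 5xSTS time. The two agree only if 5xSTS were rescored so that higher is better, and the article does not say so.

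**The case against.** The best defence is that nothing in the analysis goes wrong. The N=155 calculation is correct for the range it names, and it does not claim power at 0.20. That value is the weak edge of an approximate band; at its midpoint of 0.35, power at N=155 exceeds 0.99. The Aim 3 section and the limitations both concede low power for small effects. The signed 5xSTS hypothesis is stated clearly in its own place, and tests are two-sided. All of this stands and limits the severity. It does not rescue the sentence that presents the power figure as matching the expected effects, and it does not remove the contrary sign.

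A reader might infer three stronger things that the documents do not support.

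- **That the performance-test correlations are claimed to rest on 155 people.** The link is by placement only: these measures are listed in the N=155 paragraph. The last paragraph of Aim 1 assigns them to the 25.
- **That the n=25 results are meant to override the primary analyses.** The emphasis sentence follows directly on the caveat about shared method variance between self-report scales, so its natural sense is type of evidence. The same paragraph twice calls these analyses exploratory and warns of wider intervals. The phrase needs tightening, but it does not set up two opposite conclusions.
- **That the conclusions are oversold or a different lead comparator is required.** The abstract, Discussion and Conclusions already speak of preliminary evidence. Promoting another objective measure, such as steps per day, would be a design preference.

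**Conclusion.** The point holds as a mismatch between the power paragraph and the hypotheses it is said to serve, plus one contradicted direction. At N=155, power at the predefined |r|=0.20 is about 71% instead of 80%. At n=25, the lower part of the 0.40-0.70 band is not covered: power at 0.40 is about 51-55%, and 80% is reached only from about 0.53. The sign given for 5xSTS conflicts with the stated hypothesis.

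The figures assume bivariate normality, unadjusted two-sided alpha of 0.05, and complete data on all 155 and all 25; any loss or multiplicity adjustment lowers them. Severity is minor to moderate. No sample, model or test changes, but the text should be right before the results are read against the a priori hypotheses.

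**What to change.** In the Aim 1 sample-size paragraph:

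- Remove performance-based measures from the N=155 power and precision text. Give the n=25 figures separately: detectable |r| about 0.53, power about 51-55% at |r|=0.40, 95% CI about 0.01 to 0.69 at r=0.40.
- State the expected 5xSTS correlation as negative, matching the hypothesis earlier in Aim 1.
- State that power is about 71% at |r|=0.20, and that 80% is reached from |r| of about 0.223 (0.23 rounded up).

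In the paragraph on performance-based comparisons, reword the emphasis sentence to agree with the exploratory status given there, in the Objectives and at the end of Aim 1. For example: these comparisons are stronger in type of evidence than the self-report ones, but are exploratory and cannot override the primary N=155 analyses.

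The cost is wording and a more modest stated power. No new data or analysis is needed.

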#### Aim 2: Racial and Ethnic Disparities in Physical Function, PA, and QoL

To examine racial and ethnic disparities in physical function, PA, personal and environmental factors, and QoL among adults with ASD, analysis of covariance models will be used to compare adjusted mean outcomes between non-Hispanic White participants and participants from racial and ethnic minoritized groups. Covariates such as sex and autism severity will be included as appropriate to reduce confounding. If analyses are expanded to include more than 2 racial and ethnic groups, omnibus models will first be conducted, followed by multiplicity-adjusted pairwise comparisons where the overall test is statistically significant. Effect sizes and 95% CIs will be reported alongside *P* values. The planned sample size of 155 participants is expected to provide adequate power to detect medium-sized effects and to generate preliminary disparity estimates for future studies [63].

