### Recruitment

To target the recruitment of adults with ASD from underrepresented racial and ethnic groups, we will implement a multipronged strategy in collaboration with the SPARK Research Match service. Research Match, an integrated service of the Simons Foundation Autism Research Initiative (SFARI), enables approved investigators to recontact SPARK participants for new studies. The platform supports both remote and in-person research and streamlines enrollment by integrating invitation, eligibility screening, and survey access into a single system. Recruitment will be conducted via email outreach through SPARK’s “batched recruitment” infrastructure, which allows invitations to be distributed in waves to selected subsets of eligible participants until the enrollment targets are met. Stratified sampling will be used to ensure the representation of Black/African American and Hispanic/Latino participants, with random selection continuing until quotas of 50 participants per group are achieved.

Eligible individuals will be invited to review and electronically sign informed consent forms. We plan to enroll a total of 155 participants. All enrolled participants will complete the self-report and wearable activity monitoring components of the study. Within this overall sample, a randomized subset of 25 participants will be invited to complete the Phase 1 remote telehealth-based performance assessment session. Thus, the Phase 1 subset is nested within the full study sample.

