#### Aim 3: Associations of Physical Function, PA, Personal and Environmental Factors, and QoL, and Moderation by Race and Ethnicity

To examine the associations among physical function, PA, personal and environmental factors, and QoL, multiple linear regression analyses will be performed with QoL as the dependent variable. The primary independent variables will include PROMIS-PF and habitual PA (steps per day), with additional personal and environmental factors entered as indicated by the conceptual model. Covariates such as sex and autism severity will be included as appropriate. We hypothesize that better physical function and greater PA will be associated with better QoL. To evaluate moderation by race and ethnicity, interaction terms between race/ethnicity and physical function, as well as between race/ethnicity and PA, will be entered into the regression models. Continuous predictors will be centered prior to the creation of interaction terms to improve interpretability and reduce multicollinearity. When significant interactions are identified, simple slopes or stratified analyses will be used to further characterize the nature of the moderation effect. Model results will be reported using unstandardized and standardized regression coefficients, 95% CIs, *P* values, and model fit statistics (eg, adjusted *R*^2^). The same a priori power analysis described above applies to aim 3; although this pilot study may be underpowered to detect small effects, it is expected to provide preliminary effect size estimates to guide future research [63].

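### Aim 2 gives its stated outcome fall risk no analysis, pools two separately recruited groups into one contrast, and does not commit to adjusting for age and sex

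*Protocol article*

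**What the plan says.** The Objectives section states the second aim as: "To examine racial and ethnic disparities in physical function, PA, fall risk, and QoL among adults with ASD". The Aim 2 analysis section omits fall risk. Its heading covers physical function, PA and QoL, and its text adds personal and environmental factors. Table 1 places the STEADI fall screen under health status, so the added factors do not bring it back in.

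The Aim 2 method is analysis of covariance to "compare adjusted mean outcomes between non-Hispanic White participants and participants from racial and ethnic minoritized groups". A finer split is conditional, and nothing says what would trigger it: "If analyses are expanded to include more than 2 racial and ethnic groups, omnibus models will first be conducted". On adjustment, the section says: "Covariates such as sex and autism severity will be included as appropriate to reduce confounding".

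The Recruitment section under Methods treats the two minoritized groups as separate strata: "Stratified sampling will be used to ensure the representation of Black/African American and Hispanic/Latino participants", with a quota of 50 for each. Table 2 reports the enrolled numbers by group and sex. Eligibility spans 18 to 59 years, and Table 1 lists age among the demographics collected. Aim 3 repeats the covariate sentence ("Covariates such as sex and autism severity will be included as appropriate") but also provides for other variables, "with additional personal and environmental factors entered as indicated by the conceptual model".

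**The concern.** There are three weaknesses in the same short section.

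- **Outcome without an analysis.** One of the four disparity outcomes in the Objectives has no stated comparison, so a reader cannot tell whether it was dropped or overlooked.
- **Pooled contrast.** The study recruited two groups separately, but its default analysis compares their union with White participants. If the two groups differ from White participants by different amounts, the pooled figure describes neither. Section Aim 2 says the estimates are meant to inform future studies, and those would need the group-specific gaps. Enrolment is complete, and the choice between two and three groups is still open.
- **Loose adjustment.** Physical function and step counts can plausibly vary with age across 18 to 59 years, and Table 2 already shows that sex is unevenly distributed. Leaving age unnamed and sex optional means that part of a reported group difference could reflect either variable.

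**Working it through.** **Inputs from the article.** Table 2: White 34 (9 male), Black/African American 79 (19 male), Hispanic 40 (25 male). Two-sided alpha is 0.05 (Statistical Data Analysis Plan). The quota is 50 per minoritized group. The single Asian participant is left out below; including that person (34 vs 120) does not change the rounded power.

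**The plan's own statement.** Aim 2 says 155 participants give adequate power for medium effects, without a number. Taking medium as d = 0.5 and two equal groups, ANCOVA power is 87%. With the enrolled 34 vs 119 it is 72%.

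**Male share.**
- White: 9/34 = 26.5%
- Black: 19/79 = 24.1%
- Hispanic: 25/40 = 62.5%
- Black and Hispanic pooled: 44/119 = 37.0%

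**Mixture.** Ignoring covariates, pooled gap = (79 × Black gap + 40 × Hispanic gap)/119, so the weights are 79/119 = 66% and 40/119 = 34%.
- Gaps of 0.5 and 0 SD: 0.664 × 0.5 = 0.33 SD.
- Gaps of 0.5 and −0.5 SD: 0.332 − 0.168 = 0.16 SD.
- Had both quotas been filled at exactly 50, the first pair would have given 0.25 SD. The same true gaps give a different answer because enrolment differed.

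**Power.** For two groups I used the noncentral t with noncentrality d × √(n1·n2/(n1+n2)) and two covariates. The three-group test uses the noncentral F. Both ignore any correlation between group and covariates and any variance that the covariates explain.

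| Comparison | Noncentrality | Power |
|---|---|---|
| Pooled vs White, gaps 0.5 and 0 (d = 0.33) | 0.332 × 5.142 = 1.71 | 40% |
| Pooled vs White, both gaps 0.5 | 0.5 × 5.142 = 2.57 | 72% |
| Three-group omnibus, both gaps 0.5 | 0.25 × 34 × 119/153 = 6.61 | 62% |
| Black vs White, gap 0.5 | 0.5 × 4.875 = 2.44 | 68% |
| Hispanic vs White, gap 0.5 | 0.5 × 4.287 = 2.14 | 56% |

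A third covariate leaves the pooled figure at 72%, so adding age costs essentially nothing.

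**Sex, if left out.** Bias = assumed sex effect × difference in male share. For a sex effect of 0.5 SD:
- pooled vs White: 0.5 × (0.370 − 0.265) = 0.05 SD;
- Hispanic vs White: 0.5 × (0.625 − 0.265) = 0.18 SD.

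For sex effects of 0.2 to 0.8 SD the ranges are 0.02 to 0.08 SD and 0.07 to 0.29 SD.

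**Age, if left out.** The article gives no ages by group, so this is assumption only. Bias = (age difference/age SD) × age–outcome correlation. A group difference of 3 to 8 years, an age SD of 11 and a correlation of 0.1 to 0.4 give 0.03 to 0.29 SD.

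**The case against.** The best defence is that this is a pilot with only 34 White participants. Pooling gives the most power when both groups differ from White by a similar amount (72% against 62% for the omnibus test at 0.5 SD). The article already describes a three-group analysis with multiplicity-adjusted pairwise comparisons, and the quotas are justified by representation, which does not bind the study to separate contrasts. This stands as a reason to keep the pooled contrast. It does not justify leaving the group structure open once enrolment is known.

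A second defence is that the covariate list is illustrative and a full list may sit in an analysis plan that is not shown. That is fair. Age may be intended, and the point here is only that the published wording does not commit to it.

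Four stronger readings are tempting and are not supported:

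- **That the disparity estimate is confounded.** Sex is a named covariate, the planned pooled contrast is only mildly unbalanced on sex, and no age imbalance is documented. The 24.1% and 62.5% male shares show that the pooled groups are unlike, not that the estimate is biased.
- **That a three-group test roughly doubles power.** With gaps of 0.5 and 0 SD the omnibus test has 79% power against 40% for the pooled contrast, but much of that comes from the Black–Hispanic difference. Black vs White alone has 68%.
- **That ANCOVA cannot handle fall risk.** STEADI yields a total score, which ANCOVA can model. Only the classification at a score of 4 or more needs a binary model.
- **That Aim 3 has the same fault.** Its model admits personal and environmental factors, and Table 1 classes age there.

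**Conclusion.** The point holds for Aim 2. The missing fall-risk analysis is a plain mismatch between the Objectives and the Aim 2 analysis and rests on no assumption. The 66:34 weighting follows from Table 2, apart from small shifts when covariates are added. How much it matters depends on unknown group gaps: nothing is lost if they are equal, while gaps of 0.5 and 0 SD are reported as 0.33 SD with 40% power. For age and sex, the article shows a risk and no actual bias. The sex figures rest on an assumed effect and on sex being omitted, and the age figures are entirely assumed. All of this should be settled before the Aim 2 analysis is run, though none of it undermines the study.

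**What to change.** Before analysis, rewrite Aim 2 as follows.

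1. Fit one model per outcome with a three-level group factor (White, Black, Hispanic), with age and sex always included.
2. Report Black vs White and Hispanic vs White as estimates with 95% CIs. With power of about 68% and 56% at 0.5 SD, estimation suits them better than testing.
3. Keep the pooled White vs minoritized contrast, computed from the same model.
4. Add fall risk to the Aim 2 outcomes. Use the STEADI total score in the same model and, if the classification at 4 or more is also compared, modified Poisson or logistic regression with the same covariates.

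Naming age in Aim 3 is optional.

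The cost is wording and a little analysis, using variables already planned for collection. The one statistical drawback is that the omnibus test is weaker (62% against 72%) if both groups differ from White by the same 0.5 SD. The retained pooled contrast covers that case.
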